## Abstract

**Background:**

Prolonged latent phase of labour often results in a traumatic birth experience. Prolonged labour is associated with more operative deliveries, haemorrhage, fetal asphyxia and poor birth experience. Women with prolonged labour in a former pregnancy more often demand caesarean section in the next, due to their negative birth experience. *“*Proactive support of labour” is an alternative method, developed to counteract prolonged labour. There are little research and no randomized controlled study that compare *proactive* to *standard* labour support.

**Methods/Design:**

A prospective, non-blinded, randomized, single-centre, clinical trial where we compare proactive support to standard support of labour in a university hospital setting.

Inclusion criteria: latent phase of labour, non-pathologic pregnancy. Robson group 1, with painful contractions, and fully effaced cervix, with 1–3 cm dilatation. Exclusion criteria: induction of labour, breech presentation, twin pregnancy, multi-parity, conditions that require extended surveillance before and/or during labour.

Primary outcome: spontaneous, uncomplicated vaginal delivery. After inclusion, women randomized to proactive support of labour will stay at the hospital and have one-to-one midwife support. If no progression during the next 1–2 hours, amniotomy and/or oxytocin stimulation will be started. The control group will adhere to the standard procedures for labour support: expectance until established regular contractions and 4–5 cm cervical dilatation, and then one-to-one midwife support.

**Discussion:**

The idea of proactive support of labour is to initiate early intervention when there are signs of slow progress in order to avoid protracted labour with exhaustion of the mother, the uterus and prolonged stress of the foetus. Proactive support of labour may represent a useful method to improve labour support in nulliparous women. However, evidence based on randomized controlled trials are needed in order to know whether proactive support of labour is comparable or superior to standard care. A randomized, controlled trial is described; challenges and possible clinical implications are discussed.

**Trial registration:**

The Proactive Support of Labor Study (PAF) ClinicalTrials, NCT03056313. Registered on February 17, 2017.

## Background

Poor progression of labour is associated with increased complication rates, such as instrumental delivery, caesarean section (CS) and postpartum haemorrhage [1]. For some women, traumatic birth experience leads to posttraumatic stress disorder [2], and poor birth experience may have long-term influences on the future health of both the woman and her family [3]. Dissatisfaction with birth experience may affect women’s emotional well-being and may even affect the desire to become pregnant again [4].

There is an increasing rate of caesarean sections, reflecting an international trend [5].

In Norway, about 8% of those classified in Robson Group 1 are delivered by emergency caesarean section. Robson group 1 is defined as: nulliparous women with singleton fetuses in cephalic presentation, and spontaneous start of labour at term; it represents one third of all women in labour [6].

Preventing prolonged labour in nulliparous women is important, both for the mother and for foetus [7]. For the foetus, there is an increased risk of asphyxia [8]. For the mother, prolonged labour may be an indication for emergency CS, which in nulliparous women, is the most frequent indication for emergency CS [9]. Prolonged labour is an important cause of fear of childbirth and demand for caesarean section in the next pregnancy. Of all the CSs on maternal demand in the second pregnancy, 70% were due to traumatic birth experience in the first pregnancy [10].

The onset of the active phase of labour is defined as 4–5 cm cervical dilatation and regular contractions [11]. From the active phase, the midwife must ensure progression of labour and take actions (pain relief, amniotomy or stimulation of contractions with oxytocin) if progression is not sufficient [12].

Proactive support of labour was developed by Reuwer et al., in the Netherlands, with the purpose of preventing exhausting and prolonged labour and to facilitate a good birth experience in healthy nulliparous women [7]. Proactive support of labour focuses on the early stage of labour, the latent phase. It defines the start of the active phase of labour as 1–3 cm cervix dilatation, fully effaced cervix (< 5 mm) and painful contractions. Progress in labour is expected at this time, 1 cm per hour, according to Friedman’s curve [13]. Slow progress in the first 3 hours is a clear indication of ineffective contractions. If there is no progression during the next 1–2 hours, stimulation of the contractions should be started first with amniotomy and followed by oxytocin stimulation administered intravenously, after 1–2 hours, if regular contraction are lacking. The idea behind proactive support of labour is that intervention should be initiated early, in latent phase, (before 4 cm dilatation and regular contractions) when there is indication of slow progress. High-quality labour support includes a clear diagnosis of labour and early detection and correction of dysfunctional labour [7].

Proactive support of labour requires good communication throughout the entire process; it includes pre-labour education, psychological support, continuous personal attention and commitment. One-to-one continuous midwife support is already mandatory in early labour [7].

.Nulliparous and multiparous women have different prognoses in terms of birth progression and risk of operative birth [14]. Reuwer et al. emphasize the fundamental differences between the first and subsequent deliveries [7]. A prolonged latent phase in nulliparous women is caused by inefficient uterine contractions in about 10% of cases. Interventions have better effect in early labour, before the mother, uterus and fetus are exhausted [5]. According to Reuwer et al., labour is hard work and should take only one “working day” [7].

Today, labour support is similar in nulliparous and multiparous women. Most women in the latent phase are sent home for expectance and asked to contact the ward when the contractions increase. Active labour is defined as regular contractions and cervical dilatation of 4–5 cm [12].

### This study’s contribution to the field

This study is the first randomized controlled trial (RCT) to compare proactive labour support to standard labour support. It will shed light on the treatment of the latent phase during labour and whether proactive labour support can prevent protracted labour and result in more uncomplicated, normal deliveries.

Here we present the study design and a description of the intervention, as well as provide a detailed outline of how the intervention was planned and implemented at a delivery department in a university hospital.

### Study objectives

The main objective of this study is to examine the potential difference between proactive support of labour compared to current standard labour support, measured as number of uncomplicated, normal vaginal deliveries, and the birth experience of the mothers, as measured by the Childbirth Experience Questionnaire (CEQ) [15].

### Study hypotheses

H^0^: Women randomized to proactive labour support versus those randomized to standard labour support have similar rate of normal deliveries.

H^0^: Women randomized to proactive labour support versus those randomized to standard labour support have no difference in birth experience.

H^1^: Women randomized to proactive labour support have a higher rate of normal deliveries compared to those in the standard labour support group.

H^2^: Women randomized to proactive labour support have better birth experience compared to those in the standard labour support group.

### Study design

The present study is an open-label RCT with randomization to proactive support or standard support during labour. Women will be informed about the study at gestational week 18, and reminded at week 36/37, at an outpatient consultation. Women who meet the inclusion criteria will be included in the study and randomized at arrival to the delivery department.

## Methods/Design

### Study setting

The study takes place at St. Olav’s University Hospital in Trondheim. St. Olav’s Hospital is a public hospital, accepting 3800–4000 women in labour per year. Approximately 1500 of these women are nulliparous. In Norway, antenatal care, delivery care and postpartum care are free of charge.

Since October 2016, nulliparous women attending routine ultrasound screening, gestational week 17–19, have received written information about the study. Recruitment of participants started in March 2017. All health personnel at the delivery ward have been repeatedly informed and reminded about the study both in advance of study start and during ongoing recruitment to the study (Table 1).

**Table 1 Tab1:** Schedule for enrolment, interventions and assessment

Study period					
	Gestational week 17–19	Gestational week 36	At admission delivery dept.	During labour	6–8 weeks postpartum
Written information	x	x			
Enrolment, obtaining consent			x		
Randomization			x		
Intervention				x	
CEQ (questionnaire)					x

### Study population

Inclusion criteria are women in Robson group 1, planned for vaginal delivery. Robson group 1 represents women who are nulliparous, at term, with spontaneous labour and one foetus in cephalic presentation [9]. The pregnant women and their foetuses are healthy and in such a condition that pending treatment, i.e. return home with contractions, is safe.

Exclusion criteria are women in other Robson groups, insulin-treated diabetes, pre-eclampsia, known uterine malformation (didelphys uterus, septum in uterus, bicorn uterus)**,** other serious illnesses, such as lupus, mother’s heart disease, conditions requiring treatment during pregnancy. Exclusion criteria are also severe conditions in the foetus, such as development abnormalities, pathological Doppler, Rh-immunization, and other conditions that require extra monitoring and that prevent the midwife from practicing a pending attitude.

### Interventions

The participants in the intervention group (proactive) are defined as being in active labour. They stay at the delivery ward and receive one-to-one midwife support. A study flow chart guides the follow-up of the participant (Fig. 2). Vaginal assessment of the cervix status is performed hourly, until 3 cm dilatation of the cervix. If no progression after 1 hour, amniotomy is performed to stimulate contractions. If there is no progression, stimulation of contractions with oxytocin intravenously is initiated. We follow St. Olav’s Hospital’s standard procedure of labour management for use of oxytocin for stimulation in labour (i.e. a dosage of oxytocin, starting with a low dose). The contractions’ duration, strength and frequency are continuously assessed to prevent overstimulation.

The control group follows the standard routine at the delivery department. The women in the control group are defined as being in the latent phase. Usually, they return home to await the progression of labour and are asked to come back when they feel the need for a new assessment. They are defined as being in active labour once they reach 4–5 cm dilatation of the cervix and with regular contractions. The midwife then follows standard procedures of labour management at the delivery department and provides one-to-one support. Vaginal assessment is conducted when needed or, at the latest, after 4 hours. If the assessment shows no sign of progression of labour, amniotomy and oxytocin stimulation is initiated according to the procedures at St. Olav’s Hospital. Women in both study groups are allowed to have various pain relief treatments, for example baths, warm bags, acupuncture and epidural analgesics. The type, dosage and duration of pain relief is registered.

Women who choose not to participate in the study are treated according to standard procedures. They usually return home to wait for progression of the labour.

Normal delivery in the present study is defined as a spontaneous vaginal birth with bleeding less than 500 ml, no fever, no shoulder dystocia and no vaginal tear grade III or IV, and Apgar =/> 7 after 5 minutes. “Pathological delivery” is defined as a delivery that does not meet the criteria for “normal delivery”.

Birth experience will be evaluated by the “Childbirth Experience Questionnaire” (CEQ). The questionnaire, developed in Sweden, is to assess different aspects of first-time mothers’ childbirth experience. The questionnaire contains four dimensions: own capacity, professional support, perceived safety and participation. Multi-trait scaling analysis confirmed the fit of the model [15].

### Primary outcome

The primary outcomes of the present study are (1) the rate of normal deliveries and (2) the birth experience measured by the CEQ questionnaire.

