##### Study variables

Baseline variables are: (1) age, (2) civil status, (3) education and (4) former gynecological history (miscarriage, extra uterine pregnancy).

Variables reported during labour are: (1) number of vaginal examinations, (2) use and dosage of oxytocin before the baby is born, (3) use of spinal/epidural analgesics, (4) episiotomy, (5) mode of delivery, (6) haemorrhage, (7) perineal lacerations and (8) duration of labour.

New-born variables are: (1) weight, length and head circumference, (2) Apgar score at 5 and 10 minutes and (3) number of transmissions to neonatal intensive care unit.

The CEQ includes 22 items formulated as positive and negative statements. Each item will provide one variable in the data collection. The response format has a 4-point Likert scale, ranging from 1– totally agrees, 2 – mostly agree, 3 – mostly disagree, 4 – totally disagree. Memory of labour pain, sense of security and control are assessed with visual analogue scale (VAS). The VAS scores will be transformed to categorical values. Each item will provide one variable in the data collection [15].

No interim analyses are planned. Both types of management of labour are practiced in Norway.

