##### Statistical analyses of data

We will report data both as intention to treat and as per protocol. Per protocol data results will be considered as the clinically relevant, as the study is based on two different protocols for management of labour. The statistical program IBM SPSS Statistics for Windows version 25 will be used (IBM Corp., Armonk, NY, USA). We will report missing data as missing data. No imputation will be made.

Differences between categorical variables will be analysed by Pearson chi-square test.

*P* values < 0.05 are considered statistically significant. Continuous variables will be analysed by odds ratio and standard mean differences. Confidence intervals will be reported.

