## Discussion

This protocol describes an intervention study comparing two different methods of the treatment of the latent phase during labour. Standard management of labour is compared to proactive management of labour, which is early intervention according to a defined protocol, managing women in Robson group 1. Design, sample, primary and secondary outcomes and statistical methods are presented. The protocol is conducted in accordance with Standard Protocol Items: Recommendations for Interventional Trials (SPIRIT) 2013 statement for clinical trial protocol (Additional file 1). The study is performed in accordance with principles of Good Clinical Practice [16].

The overall aim of the study is to explore whether proactive support of labour can increase the number of normal deliveries in nulliparous women compared to standard support of labour.

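### The article names one primary outcome in its abstract and two in its main text, each tested at P < 0.05 with no rule linking them; if either could count as success, the family-wise error is about 8–10%, not 5%.

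*Protocol article*

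**What the plan says.** The parts of the protocol article do not agree on how many primary outcomes there are.

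- Abstract, Methods/Design: "Primary outcome: spontaneous, uncomplicated vaginal delivery". One outcome.
- Discussion: "The overall aim of the study is to explore whether proactive support of labour can increase the number of normal deliveries in nulliparous women". Again delivery only.
- Primary outcome section, which lists two: "The primary outcomes of the present study are (1) the rate of normal deliveries and (2) the birth experience measured by the CEQ questionnaire".
- Study objectives: the main objective covers both.
- Study hypotheses: birth experience has its own null and its own alternative, "Women randomized to proactive labour support have better birth experience compared to those in the standard labour support group", separate from the pair for delivery.

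On the error rate, Statistical analyses of data says only that P "values < 0.05 are considered statistically significant". The article gives no split, order or joint criterion.

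Power calculation uses delivery alone: 30% pathological births under standard support, a 50% reduction, 80% power and 120 women per group. There is no calculation for the CEQ.

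On the form of the CEQ, the Interventions section says "The questionnaire contains four dimensions: own capacity, professional support, perceived safety and participation". Study variables adds that there are 22 items, each recorded as a variable.

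**The concern.** With two primary outcomes, two separate hypotheses and one unadjusted threshold, a reader of the final report could take a significant result on either one as a primary success. The stated 5% would then not be the trial's chance of a false primary claim. A reader who goes by the abstract would expect a single test of delivery, and would regard a trial that was positive only on the CEQ as having missed its primary outcome. A reader who goes by the Primary outcome section could call the same trial positive. The interpretation of a split result is thus left open until the data are known.

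The sample size adds to the difficulty. If it already uses the full 0.05 for delivery, there is no alpha left for a second, independent primary claim.

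**Working it through.** **1. Reproduce the sample size.** Inputs from Power calculation: pathological births 0.30 and 0.15, power 0.80. Two-sided alpha of 0.05 is assumed, since sidedness is not stated. With pooled variance under the null, the mean proportion is 0.225 and the difference 0.15:

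n = [1.960·√(2·0.225·0.775) + 0.842·√(0.30·0.70 + 0.15·0.85)]² / 0.15²
= [1.960·0.5906 + 0.842·0.5810]² / 0.0225
= 1.646² / 0.0225 ≈ 120.5, so 121 per group.

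The unpooled form gives 118. The stated 120 is reproduced. Power at 120 per group is Φ[(0.15·√120 − 1.1575)/0.5810] = Φ(0.836) = 79.8%. The whole two-sided 0.05 has therefore gone to delivery.

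**2. Two primary tests at 0.05 each, either one counting.** If independent: 1 − 0.95² = 9.75%. The Bonferroni bound is 10%. The documents give no correlation between the test statistics, so a range was simulated from a bivariate normal (500,000 draws):

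| Assumed correlation | Family-wise error |
|---|---|
| 0.2 | 9.6% |
| 0.3 | 9.5% |
| 0.5 | 9.0% |
| 0.7 | 8.3% |

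If only errors in favour of proactive support are counted, two independent tests give 1 − 0.975² = 4.9% against 2.5%. The ratio is again about two.

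**3. Delivery plus four CEQ dimensions, each tested as primary.** If independent: 1 − 0.95⁵ = 22.6%. With assumed correlations between dimensions of 0.3 to 0.7, and of 0 or 0.3 with delivery, simulation gives about 21% down to 17%.

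**4. What each remedy does to power for delivery at 120 per group.**

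- Fixed sequence with delivery first: alpha stays 0.05, power 79.8%.
- Equal Bonferroni split: alpha 0.025, critical value 2.241. Power = Φ[(0.15·√120 − 2.241·0.5906)/0.5810] = Φ(0.550) = 70.9%. To restore 80% would need 147 per group.
- Both outcomes required: no inflation of alpha, but joint power cannot exceed 79.8% and is lower unless power for the CEQ is close to 100%. The CEQ was not sized.

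**The case against.** The strongest reply is that the article never says success on either outcome makes the trial positive. It states two hypotheses and no rule for declaring success, while the abstract, the sample size and the overall aim all put delivery first. This stands. The inflation is conditional on a reading that the text permits but does not state, and the fact that only delivery was sized is not a separate error. Even so, the reply does not settle the matter: the Primary outcome and Study hypotheses sections give the CEQ equal standing, so the article still does not say which reading applies.

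A second reply is that multiplicity handling and the choice of CEQ score commonly belong in an analysis plan or full protocol, neither of which is shown. For the choice of score this is right, and its absence here is not held against the plan. It does not resolve the conflict between abstract and main text.

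A reader might also infer that 22 item tests would be primary, because of "The CEQ includes 22 items formulated as positive and negative statements. Each item will provide one variable in the data collection". Twenty-three tests would push the error to around one half or more. The article does not support this. The sentence describes how answers are recorded, not which comparisons decide the birth-experience hypothesis, so no figure for item-level testing belongs in the finding.

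Finally, the correlations are assumptions. That is so, and it is why ranges are given.

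**Conclusion.** The concern holds in a limited form. The article contradicts itself on whether there are one or two primary outcomes, and it applies a flat 0.05 to two separately hypothesised primaries without any rule that connects them. If significance on either is taken as a primary success, the family-wise error is about 8–10% instead of 5%. The range rests on two-sided tests and an assumed correlation between 0 and 0.7. The figure of about 17–23% applies only if all four CEQ dimensions were each tested as primary, which the article neither states nor excludes. It would be too strong to say that the plan declares success at double its stated error rate, since no success rule is written down. What is established is that the rule is missing where the article itself creates the need for one.

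**What to change.** Make the abstract and the Primary outcome section name the same outcome or outcomes, and add a testing order to Statistical analyses of data:

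1. Normal delivery is tested first at two-sided 0.05.
2. The CEQ is tested confirmatorily at 0.05 only if delivery is significant, using one CEQ measure named before analysis. Otherwise it is reported descriptively.
3. The remaining CEQ dimensions and items are supportive.

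Other valid rules exist, including an alpha split or requiring both outcomes. The fixed sequence is preferred because it leaves 120 per group and about 80% power for delivery untouched, where an equal split would reduce that power to about 71%.

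The cost is more than wording. The CEQ, which has its own hypothesis and a place in the main objective, loses its stand-alone confirmatory claim whenever delivery is not significant. By May 2019, 90 women had been included in an open trial, so the change should be dated, made before analysis, and reported to the ethics committee as a protocol modification, as Ethical considerations provides. Which analysis set carries the primary test is a separate question that this change does not touch.

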### Secondary outcomes

The secondary outcomes of this study are (1) the duration of labour, in hours and minutes, (2) the number of operative deliveries (vacuum/forceps or caesarean sections), (3) use of pain relief such as epidural analgesic, (4) the use and the duration/dosage of oxytocin during labour, and (5) number of vaginal examinations provided by the midwife or gynaecologist.

